## Abstract

**Background:** The early detection of developmental conditions such as autism is vital to ensure children can access appropriate and timely evidence-based supports, services, and interventions. Children who have undetected developmental conditions early in life are more likely to develop later health, developmental, learning, and behavioral issues, which in turn can have a cumulative effect over the life course.

**Methods:** The current protocol describes a multi-site, cluster randomized control trial comparing a developmental surveillance pathway for autism to usual care, using opportunistic visits to general practitioners (GPs). Units of randomization are GP clinics across two Australian states (New South Wales and Victoria), with thirty clinics within each state, each of which will aim to recruit approximately forty children aged between ~18- and 24-months, for a total of ~2,400 participants. Children will be randomized to two clusters; namely, an autism surveillance pathway (ASP) or surveillance as usual (SaU). The screening process for the ASP arm involves primary and secondary screenings for developmental concerns for autism, using both parent and GP reports and observations. Children in both arms who show signs of developmental concerns for autism will be offered a full developmental assessment by the research team at 24 months of age to determine the efficacy of developmental surveillance in successfully identifying children with autism.

**Trial Registration:** The trial is registered with ANZCTR (ACTRN12619001200178) and reporting of the trial results will be according to recommendations in the CONSORT Statement.

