### Procedures

#### Autism Surveillance Pathway (ASP)

Parents/caregivers in the ASP arm will complete electronic versions of a participant information and consent form, a brief demographic questionnaire, in addition to the LTSAE, PEDS, and Q-CHAT-10 in the GP clinic waiting room. REDCap (NSW site) and Salesforce (VIC) will be used to manage the completion of these forms and questionnaires. An embedded algorithm on the REDCap and Salesforce platforms will score the parent responses to identify children as having developmental risk and/or high likelihood for autism, and this information from the initial assessments will be passed on automatically to the child's GP (and PN if applicable). During the consultation, the GP (or PN) will also complete the SACS Online using the Salesforce platform at both NSW and VIC sites. The ASQ:SE will be completed by parents/caregivers of children identified as having any developmental concern following completion of the LTSAE, PEDS, Q-CHAT-10, and/or SACS Online. Children will be determined as having a “high likelihood” for ASD if they: (a) are identified as “high likelihood” for autism by either the Q-CHAT-10 *or* the SACS Online assessment (regardless of the outcome of the other tools); or (b) are identified as at developmental risk by LTSAE and/or PEDS *and* ASQ:SE (but were found not at high likelihood for autism by Q-CHAT-10 and SACS Online).

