#### Surveillance as Usual (SaU) Pathway

Parents/caregivers of children in the SaU arm will complete electronic versions of the participant information and consent form and a brief demographic questionnaire. GPs (or PNs) will record any developmental screening method(s) used during the consultation using the standard template and the child's developmental risk status (i.e., high likelihood of autism).

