### Phase 3 – 30-Month Assessment Protocol

Parents/caregivers of all children recruited to both the ASP and SaU arms of the study will complete the preschool version of the Social Responsiveness Scale, Second Edition (SRS-2)(60, 61) when their child is ~30 months of age. The SRS-2 is an autism screening tool that asks parents/caregivers to rate their child's traits of autism, as seen in a naturalistic setting, on a quantitative scale. The total score provides an indication of the extent of social differences. The SRS has good internal consistency (α = 0.93) and good test-retest reliability in preschoolers (intra-class correlation = 0.74) (61, 62).

Parents/caregivers of children identified with a developmental condition from both arms will also complete a semi-structured questionnaire to evaluate the uptake of recommendations, experience of assessment/service use, disability supports, and early intervention received and parental satisfaction with the health and disability services. This will facilitate comparison between those in the ASP arm who received the assessments and recommendations using the NAG and those in the SaU arm who received routine care.

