### Statistical Analysis

#### Quantitative Analysis

The entire raw dataset will be provided to an independent biostatistician, along with the study protocol and the pre-specified statistical analysis plan, who will conduct an independent analysis of the raw data. Details of this independent statistical analysis, as well as the name and academic institution of the independent statistician and whether compensation or funding was received for conducting the analyses, will be included in the publication of the results of the study.

Descriptive statistics for outcome measures (percentage, mean, and SD) and psychometric properties of the measures (reliability, Cronbach's α) will be reported. Descriptive statistics for all parental socio-demographic will also be presented, with the expectation of no group differences. We will compare the differences between the control arm (SaU) and the intervention arm (ASP) for the following primary outcomes:

(1a). the uptake of autism developmental surveillance as indicated by the proportion of children who participated in the program;(1b). the proportion of children correctly identified by the GPs as being at “high likelihood” of autism, and later confirmed as having ASD through the “gold standard” assessment.(2) the proportion of children in both groups who received referrals following identification of developmental concerns;(3) the access and utilization of child health and developmental services will be ascertained based on the uptake of recommendations as assessed at the 30-month follow up.

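### The 30-month service outcome is collected only from children identified after randomisation by routes that differ between arms, the referral outcome has no fixed denominator, and the routine-care label for SaU conflicts with the shared research assessment

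*Protocol article*

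**What the plan says.** All references are to the protocol article.

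- **Outcomes.** Quantitative Analysis names two outcomes, among those it calls primary, for comparison between SaU and ASP. Outcome 2 is "the proportion of children in both groups who received referrals following identification of developmental concerns". Outcome 3 is access to and use of child health and developmental services, which "will be ascertained based on the uptake of recommendations as assessed at the 30-month follow up".
- **Who supplies outcome 3.** Under Phase 3 – 30-Month Assessment Protocol: "Parents/caregivers of children identified with a developmental condition from both arms will also complete a semi-structured questionnaire". Table 1 appears to place this questionnaire only in the High ASD risk column of each arm. The same section makes a wider contact for the SRS-2: "Parents/caregivers of all children recruited to both the ASP and SaU arms of the study will complete the preschool version".
- **How children are identified.** In ASP, parents complete three tools and the GP or practice nurse a fourth. The ASQ:SE follows for children "identified as having any developmental concern following completion of the LTSAE, PEDS, Q-CHAT-10, and/or SACS Online" (Procedures, Autism Surveillance Pathway). In SaU, GPs or practice nurses "will record any developmental screening method(s) used during the consultation using the standard template" (Procedures, Surveillance as Usual).
- **How SaU is described at 30 months.** Phase 3 contrasts ASP families, assessed and advised under the national guideline, with "those in the SaU arm who received routine care". The Abstract says: "Children in both arms who show signs of developmental concerns for autism will be offered a full developmental assessment by the research team". Table 1 and the Phase 2 Procedure give both arms the same 24-month battery and extend it to a random 10% of screen negatives in each.

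**The concern.** In a cluster trial of surveillance, being identified is itself an effect of the allocated arm. The Aims and Hypotheses expect ASP to change how many children are identified and how accurately. A comparison restricted to identified children therefore sets two differently selected groups against each other. If one route picks up a wider range of severity, the groups will differ in need, in the advice they receive and in service use, even if the pathway does nothing further for a child once identified. The covariates that the analysis section gives as examples (gender, maternal education, socioeconomic status) measure neither severity nor route of identification.

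The result has a practical use. The Hypotheses section says the comparison of uptake, service access and satisfaction is to inform an integrated Australian care pathway. A contrast that can point the wrong way, against a comparator described in two different ways, is a weak basis for that.

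**Working it through.** The article gives no expected rates for outcomes 2 or 3, so there is no plan figure to reproduce. The check asks whether the choice of denominator can change the conclusion.

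**Notation.** Let N be the children recruited per arm, f the number identified and r the proportion of those referred, with subscripts A (ASP) and S (SaU).

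- Difference among identified children: D_id = r_A − r_S
- Difference per recruited child: D_all = (f_A·r_A − f_S·r_S) / N
- The two have opposite signs whenever f_S/f_A < r_A/r_S < 1.

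**Inputs.**

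| Input | Value | Source |
|---|---|---|
| N | 1,200 per arm | 2,400 in total (Sample Size); equal split assumed |
| At-risk share | 30% | Introduction, where it is an upper figure from one Sydney cohort |
| f_A | 0.30 × 1,200 = 360 | assumes ASP finds every at-risk child |
| f_S | 30% to 50% of 360 = 108 to 180 | Introduction gives 30–50% for completed surveillance records; used as a proxy for detection |
| Referral | 90% if evident, 50% if subtle | assumed |
| Case mix | SaU finds only evident cases; ASP finds those and the subtle ones | assumed |

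Referral depends only on severity here, so the arms treat like children alike once they are identified.

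**SaU identifies 108.**
- ASP referrals: 108 × 0.9 + 252 × 0.5 = 97.2 + 126 = 223.2
- SaU referrals: 108 × 0.9 = 97.2
- Among identified: 223.2/360 = 62% v 90%, D_id = −28 points
- Per recruited child: 223.2/1,200 = 18.6% v 97.2/1,200 = 8.1%, D_all = +10.5 points

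**SaU identifies 180.**
- ASP referrals: 180 × 0.9 + 180 × 0.5 = 162 + 90 = 252
- SaU referrals: 180 × 0.9 = 162
- Among identified: 252/360 = 70% v 90%, D_id = −20 points
- Per recruited child: 252/1,200 = 21.0% v 162/1,200 = 13.5%, D_all = +7.5 points

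**Wider range.** Fix SaU referral at 80%, vary ASP referral from 40% to 80%, take the at-risk share as 20% or 30%, and let SaU find 30% or 50% of at-risk children. D_id then runs from −40 to 0 points and D_all from 0 to +16.8 points. The reversal is not inevitable. With ASP at 40% and SaU finding half, D_all is zero. With both arms at 80%, D_id is zero while D_all is +8.0 to +16.8 points.

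**Outcome 3.** Let u be service use among identified children and v among the rest. Use per recruited child is [f·u + (N − f)·v] / N. The questionnaire measures u only, and the article describes no 30-month service-use data from the other families. The randomised comparison therefore cannot be formed from what is collected, whatever the analysis plan says.

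**Comparator.** Phase 3 labels SaU as routine care. The Abstract, Table 1 and the Phase 2 Procedure offer flagged SaU children the same ADOS-2, ADI-R, MSEL and VABS-3 assessment by the research team at about 24 months. By the 30-month questionnaire, the SaU families who answer it have mostly been offered something beyond routine care.

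**The case against.** **Outcome 2 may already be sound.** A reader might infer that it compares only identified children. The text does not establish that: the denominator can be all children in each group, with identification merely describing which referrals count. Phase 4 also plans clinic audits counting eligible children seen and children referred. This objection stands, and for outcome 2 the point reduces to an unfixed denominator. Fixing a denominator is often left to the analysis plan, but here the two readings can give opposite answers. The audits cover all attending children through deidentified reports, so they support a clinic-level view but do not say which denominator outcome 2 uses.

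**The illustration is constructed.** This stands too. The referral rates and case mix are assumptions, and the article nowhere says that ASP will flag milder children. The figures show that a reversal is possible; they do not forecast one.

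**Identified with a developmental condition may mean confirmed at 24 months.** In that case severity would differ less between arms than among flagged children. Entry would still depend on arm, because apart from the 10% sample of screen negatives a child reaches that assessment through the arm's own route. Table 1 appears to point to the flag instead.

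**Uptake of recommendations exists only for families given recommendations.** This is true, and it is why the measure among identified children deserves reporting. It answers a different question from the randomised one.

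**The shared assessment is the reference standard needed for outcome 1b and is openly described.** This is correct. A reader might infer that it voids the 30-month comparison. It does not: the surveillance step still differs by arm. Dilution is the supportable claim.

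**The two formal primary hypotheses concern surveillance completion and correct identification.** They are untouched by this point. Outcomes 2 and 3 are nevertheless listed as primary in the analysis section.

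**Conclusion.** The point holds in three parts of unequal strength.

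1. **Outcome 3: firm.** Its data come only from a group formed after randomisation by different routes in the two arms. The between-arm contrast is open to selection bias, possibly in sign, and no analysis plan can recover answers from families who were never asked.
2. **Outcome 2: an ambiguity with consequences.** Under the stated assumptions, ASP is 20 to 28 points worse on one reading and 7.5 to 10.5 points better on the other. The size depends on the assumed referral rates, the equal split and the detection proxy. The condition for reversal is general.
3. **Routine-care label: an internal conflict.** Phase 3 disagrees with the Abstract, Table 1 and the Phase 2 Procedure. The shared assessment may prompt service use in SaU and so shrink the difference seen at 30 months.

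This should be corrected, but it does not threaten the surveillance-completion or correct-identification hypotheses.

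**What to change.** - **Denominator.** State that the between-arm comparison of outcomes 2 and 3 uses all recruited children in each arm. For outcome 2, a child for whom no concern was raised counts as not referred.
- **Data for outcome 3.** Add a few service-use items to the 30-month online SRS-2 contact, which already goes to every recruited family.
- **Results among identified children.** Keep referral proportions and uptake of recommendations in this group as descriptive only, and say that the groups are not comparable by randomisation.
- **Who receives the full questionnaire.** Reconcile the Phase 3 wording with the Table 1 columns, stating whether a clinic flag or a confirmed condition is meant.
- **Comparator.** Reword Phase 3 to agree with the Abstract, Table 1 and the Phase 2 Procedure: SaU is usual GP detection followed by the shared research assessment. Limit the 30-month conclusion to that contrast.

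The cost is wording in the protocol and analysis plan, a few extra online items and a small added burden for families not otherwise asked about services. Sample size and clinical procedures do not change.

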Whilst advances have been made in developing effective early interventions for ASD, significant barriers exist in accessing such intervention early within the period of greatest responsiveness to support and intervention (25). There are a few studies that have explored processes for the detection of developmental vulnerability in early life and barriers to accessing early intervention. One such study is the Watch Me Grow (WMG) program (26), conducted in a birth cohort of two thousand children in Sydney, Australia, in partnership with the New South Wales (NSW) state government health department. The WMG study (26–29) revealed that up to 30% of children are at developmental risk by their 18-month “well-child” check, but only 30–50% of these children attending primary health care (general practitioners—GPs, and child and family health nurses—CFHNs) have their developmental surveillance record completed. This is in keeping with the findings from a population health survey in NSW, Australia (30) that found that only around 66% of children attend “well-child” checks until around 12 months of age, and that this rate drops to 20% between 1 and 4 years of age. Thus, the period from 12 months to 5 years of age is a critical “silent” period for assessing a range of developmental and behavioral concerns, including speech and language difficulties and ASD. However, it is to be noted that across Australia there is considerable variability between states in children accessing developmental surveillance (26). For example, while NSW has a developmental surveillance attendance rate of 30% at 18 months (31), attendance is much higher in Victoria (VIC) at 74.2% (32).

Further, the WMG study found evidence of an “inverse care law,” whereby those at highest risk (such as children whose mothers were born overseas, or with lower maternal education and income levels) for developmental delay were the least likely to access the developmental surveillance program (27, 29). Qualitative analyses also indicated that facilitators to accessing developmental surveillance for families included proximity to the center, continuity of care, visits being combined with another recommended service (e.g., immunization) and language concordance by the provider (33). Access to good developmental surveillance programs could lead to better support for families, particularly those who have complex and multiple social risk factors.

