## Methods and Analysis

### Study Design

A multi-site, cluster RCT with a qualitative component will be implemented (Figure 1). Using a minimization randomization procedure over size of GP clinic (<4 GPs or ≥4) and site (NSW or VIC), the participating GP clinics within the two Australian States (NSW and VIC) will be allocated to one of two arms:

Surveillance as Usual (SaU), representing current practice, orASD surveillance pathway (ASP), which will implement the “enhanced surveillance” protocol.

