### Analytical Plan

#### Sample Size

The total sample size of children recruited into the study will be 2,400 children across the two sites, which will provide adequate statistical power to address the study hypotheses. This sample will enable us to achieve 80% power to detect a difference between the two group means of 0.0935 standard deviations (SD) using a significance level of 0.05. In analyses comparing the smallest anticipated subgroups (as small as 20% of the original group sizes), a mean difference of 0.21 standard deviations will be detectable retaining the same power and significance levels. For the qualitative component of the study, it is envisaged that approximately twenty participants (GPs and PNs) will be enough to obtain thematic data saturation.

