analysis to determine the overall effectiveness of the “enhanced” autism surveillance pathway will involve comparison between the two groups, adjusting for potential confounders which are significantly different between clusters or strongly associated with the outcome variable, such as gender, maternal education, and socioeconomic status. Outcome group differences in the uptake of developmental surveillance, completion of surveillance tools and accurate identification of children at high likelihood of autism and diagnosed with ASD will be investigated using risk difference (RD) with 95% confidence interval (CI) and, where indicated, kappa coefficients. We will use generalized estimating equations (GEE) modeling to identify if there are factors other than the intervention that may also explain differences between the two arms. The intervention will be considered as a fixed effect and cluster assignment as a random effect, to account for group membership. Such modeling techniques adjust for clustering and also allow the inclusion of both cluster- and individual-level covariates. Statistical analysis will be carried out using IBM SPSS Statistics version 26 (66), Mplus 7.1 (67), and R v4.0.1 (68).

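### Adjustment covariates are chosen by an ambiguous, data-driven rule, and the minimisation factors (state, clinic size) are not fixed in the model

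*Protocol article*

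**What the plan says.** The protocol article, under Quantitative Analysis, states the rule for the overall effectiveness comparison as "adjusting for potential confounders which are significantly different between clusters or strongly associated with the outcome variable". It then mentions the child's gender, the mother's education and socioeconomic status; these three variables are examples, not a list. The same paragraph says that the models can take covariates at both cluster and individual level, but it names no cluster-level covariate.

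Under Study Design, clinics are allocated "Using a minimization randomization procedure over size of GP clinic (<4 GPs or ≥4) and site (NSW or VIC"). The analysis text mentions neither factor.

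The Introduction reports a large gap between the states in routine surveillance: "while NSW has a developmental surveillance attendance rate of 30% at 18 months (31), attendance is much higher in Victoria (VIC) at 74.2"%.

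The article uses the word *clusters* in two senses. The Abstract says that children are randomised to two clusters, meaning the arms. Participants and Setting uses the word for the GP clinics, about 30 per state. A pre-specified statistical analysis plan is mentioned but is not shown.

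**The concern.** The rule lets the data decide what the adjusted treatment effect is adjusted for. Two statisticians could both follow it faithfully and report different adjusted effects. That matters here because the raw data go to an independent biostatistician for a separate analysis.

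The first criterion also fails on either reading of *clusters*. Differences between clinics are expected for any variable that varies by area, and they say nothing about imbalance between the arms. A significant difference between the arms, absent recruitment bias, is a chance event, and its p-value does not show whether adjustment would help. Minimisation makes state and clinic size nearly equal across arms, so a test between arms would seldom pick them.

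That leaves the second criterion, strong association with the outcome, as the only route by which the two allocation factors reliably enter the model. *Strong* is not defined. If a prognostic allocation factor is left out, the estimate keeps the benefit of balance, but the model-based or clustered standard error still counts the between-state variation that minimisation removed. The interval is then too wide and the test too conservative.

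**Working it through.** The plan gives no figure for the effect of adjustment, so there is none to reproduce. Its stated detectable difference of 0.0935 SD involves no covariates and is not used here.

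**Inputs from the protocol article.** About 60 clinics, 30 per state, and about 40 children per clinic (Participants and Setting). State rates of 30% and 74.2% (Introduction), used only as an illustration.

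**Assumptions.** 1:1 allocation, so 15 clinics per arm per state. The article gives no ICC, so a range is shown.

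**1. What the first criterion would select.**

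*Clusters read as clinics.* A 5% one-way F-test over 60 clinics has 59 and 2,340 degrees of freedom and a critical value of 1.327. For a covariate with intraclass correlation ρ, the F statistic is inflated by 1 + 40ρ/(1 − ρ). The chance of selection is then:
- ρ = 0.01: about 60%
- ρ = 0.02: 94%
- ρ = 0.05: above 99.9%

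*Clusters read as arms.* If the baseline test ignores clustering, the chance of a spurious difference is 2Φ(−1.96/√DE), with DE = 1 + 39ρ:
- ρ = 0.02: DE = 1.78, giving 14%
- ρ = 0.05: DE = 2.95, giving 25%

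This applies to covariates that were not balanced by design. State and clinic size are minimised and would rarely be flagged.

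**2. Standard error with and without state.** Let p₁ and p₂ be the state rates.
- Within-state variance of a clinic proportion: W = mean[p(1 − p)] × (ICC + (1 − ICC)/40)
- Extra variance if state is omitted: B = ((p₂ − p₁)/2)²
- SE of the risk difference, 30 clinics per arm: √(2W/30) with state, √(2(W + B)/30) without

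For 30% and 74.2%, mean[p(1 − p)] = (0.2100 + 0.1914)/2 = 0.2007 and B = 0.221² = 0.0488.

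| ICC (assumed) | W | SE with state | SE without state | Ratio |
|---|---|---|---|---|
| 0.02 | 0.0089 | 0.024 | 0.062 | 2.54 |
| 0.05 | 0.0148 | 0.031 | 0.065 | 2.07 |
| 0.10 | 0.0246 | 0.040 | 0.070 | 1.73 |

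**3. The same formula with smaller differences between states.**
- 40% versus 60%, ICC 0.05: ratio 1.25
- 45% versus 55%, ICC 0.05: W = 0.2475 × 0.07375 = 0.01825, B = 0.0025, ratio √(0.02075/0.01825) = 1.07
- 1% versus 2%, as might apply to outcome 1b, ICC 0.01 to 0.05: ratio 1.02 to 1.01

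**4. What the second criterion would do.** Clinic-level simulation, beta-binomial, 4,000 runs per setting, ICC 0.05, reading strong association as p < 0.05 for state. Power is for a true 10-point difference.

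| State rates | Runs selecting state | Power: omitted / always in / by rule | Type I error: omitted / always in / by rule |
|---|---|---|---|
| 30%, 74.2% | 100% | 17% / 89% / 89% | 0.0% / 4.9% / 4.9% |
| 47%, 53% | about 40% | 80% / 81% / 81% | 4.2% / 4.7% / 4.7% |

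On that reading the rule recovers state when state matters greatly, and selects it erratically when it matters little. No figure can be given for clinic size, because the article reports nothing about its effect.

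**The case against.** The strongest reply is that the rule does not exclude state or clinic size. The examples are open-ended, cluster-level covariates are allowed, and a strongly prognostic state would qualify. In the setting with the largest loss, the rule read as p < 0.05 included state in every run and performed as well as fixed adjustment. This stands. A reader might infer that the plan throws away most of the precision that its allocation buys, or that power would be about 17%. Those figures describe an analysis with state omitted, and the article does not say that state is omitted.

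The 30% and 74.2% are routine attendance rates at 18 months. They are not rates of the trial's outcomes, which concern autism surveillance through the GP clinic and confirmed identification. They do not establish state as the strongest predictor of those outcomes, and no rival predictor has a comparable figure. This also stands.

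A reader might further infer that the type I error rate is compromised. That is not shown. Omitting a balanced factor makes the test conservative, and the simulated selection on state alone held its level. Selection among several covariates was not examined.

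Last, a covariate list commonly belongs in the analysis plan, so not naming the two factors would be a weak point if it stood alone. But the article does more than stay silent. It publishes a selection rule, which the analysis plan must either follow or contradict.

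**Conclusion.** The point holds as a badly chosen method, not as a demonstrated loss. The published rule is data-driven, has no threshold or closed list, and rests on a word that the article uses in two senses. Neither sense gives a sound criterion. The two factors on which clinics are allocated depend on an undefined screen to enter the model.

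The size is conditional. If state were omitted, and if the state gap in the primary outcome resembled the gap in routine attendance, the standard error would be about 1.7 to 2.5 times too large for ICCs of 0.10 down to 0.02. With a modest state difference or a rare outcome the effect is a few per cent or less. The ICCs and the equal split of clinics are assumptions, and no size can be put on clinic size. Fixed adjustment secures whatever gain there is without depending on a reading of the rule, so the change should be made.

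**What to change.** Replace the selection rule with a fixed one: all primary analyses adjust for state (NSW or VIC) and clinic size (<4 or ≥4 GPs), plus a short list of prognostic covariates named before the data are seen and kept regardless of baseline tests or observed association with the outcome. Child sex is a natural entry. Maternal education and socioeconomic status can join it where the enrolment questionnaire collects them. The article describes that questionnaire only as brief and demographic, so this must be checked first. Where an outcome uses only clinic-level audit counts, adjust for the two minimisation factors alone. Use *cluster* for clinics and *arm* for treatment groups throughout, including the Abstract.

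The cost is a sentence or two in the analysis plan and a few degrees of freedom among about 60 clinics. State and clinic size are already held for the allocation.
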